HoryzonsCa will be acceptable to patients. Our conceptualization of acceptability is partially informed by the TAM [37,38], which posits that attitudes toward using a technology influence intention (“acceptance”) to use a technology, which is a direct determinant of behavior [37,38]. The attitude construct is composed of perceived usefulness (an individual’s perception that using an information technology [IT] system will be helpful to them) and perceived ease of use (an individual’s perception that using an IT system will be free of effort) [38]. Patients’ acceptance regarding the use of technologies in health care delivery has been extensively assessed using the TAM model and its derivatives, which highlight the importance of considering factors beyond the individual’s attitudes [41-44]. As such, we also include the concept of adoption in our conceptualization of acceptability, which “is defined as the intention, initial decision, or action to try or employ an innovation or evidence-based practice” [45]. Thus, using this combined understanding of acceptability, in this study, the intervention will be considered acceptable if at least 70% of participants provide positive reports on general experience of the platform, 60% provide positive reports on perceived usefulness (helpfulness), 60% provide positive reports on ease of use, and 60% log onto the site at least 4 times over the 8-week follow-up. These percentages are hypothesized based on the results obtained from the original Horyzons pilot study [27]. We will also determine acceptability through qualitatively assessing perceptions of HoryzonsCa in relation to likes, dislikes, perceived barriers and facilitators to using the platform, and ease of use/experiences of navigating and using its key features (eg, various psychoeducational modules or café) and through exploratory analysis of website use analytics.To assess the safety of the HoryzonsCa platform. *Secondary hypothesis:* HoryzonsCa will be safe, defined as no adverse events, reports, or incidents (eg, hospitalization, suicidal ideation, or disclosure to treatment team regarding harm) related to use of the platform from baseline assessment to 8 weeks follow-up, and at least 70% of participants report that they agree or strongly agree with the perceived safety of the platform and perceived confidentiality of information shared on the platform. We will also determine safety through qualitatively assessing perceptions of the HoryzonsCa platform (eg, experiences, concerns).To assess the potential efficacy of the HoryzonsCa intervention/platform. *Secondary hypotheses:* Participants will show moderate to large improvements (Cohen *d*≥0.5) on measures of social functioning (Social and Occupational Functioning Assessment Scale; Personal and Social Performance Scale) and either improvement of 1 point or no deterioration on the Clinical Global Impression Scale, from baseline to 8 weeks follow-up, as our primary foci for assessing potential efficacy. We will also assess for improvements in social support, self-esteem and perceived strengths, and symptoms. The analysis will help determine pre-post effect sizes on a number of variables conceptually targeted by the platform. These effect sizes will be used in a future clinical trial (eg, randomized controlled trial) for the purpose of statistical power calculation and estimation of sample size.

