### Participants, Sample Size Considerations, Recruitment, and Orientation Process

The target sample is 20 to 25 participants that are patients receiving services from PEPP-Montreal. This sample size was determined by the following factors: feasibility of participant recruitment within a 2- to 3-month time frame, budget related to staffing of moderators, and ensuring adequate number of active users on the platform for the social networking features to function effectively. This sample size has also shown to be sufficient to pilot-test the feasibility and acceptability of Horyzons, as illustrated in the prior pilot study [27] while also acknowledging the limitation of this small sample size for efficacy testing (which is not the main objective of this pilot study). Participant inclusion and exclusion criteria are presented in Textboxes 1 and 2, respectively.

Inclusion criteria.

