### Analysis Plan

Following the convergent mixed methods model, the quantitative and qualitative data will first be analyzed separately and then considered for an integrated analysis of the findings [58]. The quantitative data (including website use data) will first be assessed using descriptive statistics (eg, frequencies). Specifically, to evaluate the acceptability and safety of HoryzonsCa, we will analyze quantitative feedback from the HC-AUSI-Q and website use by calculating proportions (ie, percentage of participants who indicate agree or strongly agree for specific items related to acceptability and safety; percentage of participants with at least 4 log-ins over the 8 weeks follow-up). To assess the potential efficacy of HoryzonsCa, paired samples *t* tests will be conducted on social functioning and clinical measures, and within-group effect sizes (Cohen *d*) will be reported for statistically significant changes between baseline and the 8 weeks follow-up. We will make Bonferroni corrections to reduce the inflation of alpha for multiple comparisons and determine a minimal clinically important difference to detect important changes over time. In addition, exploratory analysis of potential meditators and moderators of treatment effects will be conducted; for example, we will analyze the associations between website use and treatment effects to estimate the moderating role of website use. We will conduct the checks of assumptions prior to conducting analysis, including normality of the data, and will transform the data if needed. Two members of the research team (eg, a postdoctoral fellow and a research assistant) will review data quality (eg, missing data) and determine the best approach (eg, multiple imputation) to handle the missing data in consultation with a statistician and senior members of the research team. Quantitative data analysis will be supported using SPSS (IBM Corp; or R [R Foundation for Statistical Computing]).

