## Results

This study was funded by the Brain and Behavior Research Foundation (United States), Quebec Health Research Funding Agency (Canada), and the Canada Research Chairs Program (Canada), and was approved by the Research Ethics Board of the Centre intégré universitaire de santé et de services sociaux de l'Ouest-de-l'Île-de-Montréal on April 11, 2018 (#IUSMD 17-54). The study was registered as a clinical trial at [60] (ISRCTN43182105). Recruitment was initiated on May 10, 2018, and data collection occurred between August 16, 2018, to April 29, 2019. A total of 48 individuals were approached for the study, from which 20 were excluded (17 declined to participate, 1 was not reachable, 1 did not meet inclusion criteria, and 1 met exclusion criteria). The 28 remaining individuals provided informed consent and were invited to complete a baseline assessment, from which 4 did not attend for various reasons (eg, no longer interested, no longer attending clinic, or not feeling well). Among the 24 participants that completed the baseline assessment, 3 dropped out of the study before being given access to the intervention, and 1 was excluded from the intervention soon after team discussion of the baseline assessment due to not meeting inclusion criteria (ie, clinical stability). Upon completion of the baseline assessment and confirmation of eligibility criteria, a final sample of 20 participants were given access to the intervention and none of these were lost at 8 weeks follow-up. Participants were recruited over a 9-month duration (which was 3 times longer than our originally anticipated 3-month timeline), with a recruitment rate of approximately 3 participants per month. A total of 9 participants attended the focus group meetings of approximately 120 minutes each session (4 attended more than once). No adverse events related to the intervention occurred during the live pilot implementation. Further details on the results are expected to be submitted for publication in 2021.

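### The two-part safety rule ends in the verdict safe, but with 20 users zero related events leaves risks up to about 14% (one-sided 95%) open, and the article never says so

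*Protocol article*

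**What the plan says.** The second objective, under Objectives and Hypotheses, sets a two-part rule. The first part is an event count: "HoryzonsCa will be safe, defined as no adverse events, reports, or incidents", restricted to those "related to use of the platform from baseline assessment to 8 weeks follow-up". The second, joined to the first by *and*, is a perception criterion: "at least 70% of participants report that they agree or strongly agree with the perceived safety of the platform", with confidentiality of shared information treated the same way. Qualitative assessment of experiences and concerns is added.

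On size, the article states: "The target sample is 20 to 25 participants". The basis is practical: "This sample size was determined by the following factors: feasibility of participant recruitment within a 2- to 3-month time frame", plus the moderator budget and having enough active users for the social network to work. The Results section reports "a final sample of 20 participants were given access to the intervention and none of these were lost at 8 weeks follow-up", and that no adverse event related to the intervention occurred.

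On analysis, the plan reads: "to evaluate the acceptability and safety of HoryzonsCa, we will analyze quantitative feedback from the HC-AUSI-Q and website use by calculating proportions". That sentence covers the questionnaire and log-in data. For events, the Safety subsection says that they were monitored and counted, that relatedness was judged by the research and moderation team from documentation of each event, and that all events went to the ethics board. Neither place gives an acceptable event rate or a confidence level for the event criterion.

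**The concern.** The rule turns an observed count of zero, with a favourable opinion score, into a categorical conclusion about the platform. A zero count in a small group describes that group. What it says about future users depends on how many people could have had an event, and here that is 20.

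The events named as examples include hospitalization and suicidal ideation, so a reader will take the word safe seriously. The findings are also meant to inform decisions on scaling up the evaluation and the implementation of the intervention. If the rule is applied as written, the word safe is carried forward without the range of risks that the data leave open.

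The existing caveats do not fill the gap. The sample-size section links the small sample to efficacy testing. Strengths and Limitations links it to detecting treatment effects and impact, and links the caution on safety to the 8-week follow-up.

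**Working it through.** **Inputs.** Exposed users: 20, none lost (Results). Related adverse events reported: 0 (Results); I take this to mean that no related report or incident occurred either. Planned range: 20 to 25 (sample-size section). Perception threshold: 70%, so 14 of 20 (Objectives and Hypotheses). Confidence level: none stated, so 95% is assumed. Acceptable event rate: none stated, so the true risks used below are illustrative.

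The article gives no bound or precision figure for safety, so there is no figure of its own to reproduce first.

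**Step 1: what zero events exclude.** The exact binomial upper limit for 0 of n is 1 − α^(1/n), with α = 0.05 for a one-sided and 0.025 for a two-sided 95% limit.

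| n | One-sided 95% | Two-sided 95% |
|---|---|---|
| 20 | 1 − 0.05^(1/20) = 13.9% (about 1 in 7) | 1 − 0.025^(1/20) = 16.8% (about 1 in 6) |
| 25 | 1 − 0.05^(1/25) = 11.3% (about 1 in 9) | 1 − 0.025^(1/25) = 13.7% (about 1 in 7) |

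As a rough check, the rule of three gives 3/20 = 15.0%.

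**Step 2: how often the event criterion alone is met.** With a true risk p per user over 8 weeks, and independent users, P(no event) = (1 − p)^20.

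| True risk p | P(no event in 20) |
|---|---|
| 1% | 0.99^20 = 82% |
| 3% | 0.97^20 = 54% |
| 5% | 0.95^20 = 36% |
| 10% | 0.90^20 = 12% |

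The probability falls to one half at p = 1 − 0.5^(1/20) = 3.4%. The first row also shows the opposite error: at a true risk of 1%, the criterion fails 18% of the time.

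**Step 3: whether the second criterion helps.** It asks whether participants felt safe and thought their information confidential. No agreement percentage yields an upper limit on the event rate. It is also imprecise in itself: 14 of 20 has an exact 95% interval of 46% to 88%.

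**Step 4: whether the caveats cover it.** The article's statements on small sample size concern efficacy, treatment effects and impact. Its statement on caution with the safety findings gives follow-up length as the reason. No sentence connects 20 users with the meaning of zero events.

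**The case against.** The strongest reply is that this is a pilot and is described as one. The Conclusions call the evidence preliminary, the limitations list the small sample and ask for caution on safety, and the Results say only that no related adverse event occurred. The word safe appears in a hypothesis with an operational definition, not in a claim about a population rate. For a given sample size, zero is the strictest count that can be required. Whether a count is printed with an interval is commonly left to an analysis plan that is not shown here.

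Much of this stands. It rules out several stronger readings that a reader might infer:

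- *Zero events alone earns the label.* It does not. The perception criterion must also be met, so the percentages in Step 2 are chances of meeting the event criterion, and at most upper bounds on the chance of reaching the verdict.
- *Zero is the likely result even when the risk is important.* Zero is more likely than not only below a true risk of about 3.4%. At 5% the event criterion fails 64% of the time, and at 10% it fails 88% of the time. The documents also name no rate that counts as important.
- *The article presents safety as established, or the pilot is too small.* The first is contradicted by its own hedges. The second does not follow, since the sample size was set openly on practical grounds.

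What does not stand is the appeal to an unseen analysis plan. The definition is fixed in this article, and an interval reported elsewhere would leave the verdict as worded. The general hedges do not tell the reader what 20 users can and cannot exclude.

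**Conclusion.** The concern holds in a limited form. The rule as written leads from zero related events and 70% agreement to a categorical verdict that 20 users cannot support. Zero of 20 leaves risks per user of up to 13.9% (one-sided) or 16.8% (two-sided) over 8 weeks compatible with the data. Reaching the top of the target range would have lowered this only to 11.3% or 13.7%.

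These figures rest on an assumed 95% level, on independence between users, and on the reported zero covering related reports and incidents as well as adverse events. The true risks of 3%, 5% and 10% only illustrate how the event criterion behaves. The fault lies in the word attached to the result and in a limitation left unstated. It does not lie in the size of the pilot, the monitoring of events or the choice of criteria.

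**What to change.** Keep both criteria. Replace the conclusion *safe* with wording such as: *no related event observed in 20 users over 8 weeks (exact 95% upper limit 13.9% one-sided, 16.8% two-sided); no safety signal, but risks below that limit are not excluded*. Choose one of the two limits and state which. Report the perception result beside it as a separate finding.

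In Strengths and Limitations, give the small sample as a reason for caution on the safety findings, alongside the short follow-up. The same limit for events of any cause could be added but is optional.

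The cost is one binomial limit, two sentences and a more modest safety claim. No new data are needed, and the article says that analysis and reporting were still in process.

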### The Horyzons Intervention Platform

Members of our team have developed an innovative web-based therapeutic intervention platform, called Horyzons, designed to sustain the treatment benefits of early intervention for psychosis and to promote long-term social functioning [27]. This intervention delivers evidence- and strengths-based targeted psychosocial interventions and is enhanced by a moderated online social networking environment. Youth diagnosed with FEP are guided through interactive games to identify, discuss, and develop key personal strengths in an online environment and in real life to address relapse risk factors and psychological well-being.

Specifically, Horyzons consists of *interactive psychosocial interventions* that are informed by evidence-based psychosocial interventions targeting key risk factors and salient domains in the early recovery process (including psychoeducation, vocational recovery, early warning signs of relapse, depression, social anxiety, personal strengths). Youth with FEP are prompted to practice newly acquired skills through over 350 purpose-developed behavioral activities, which are designed to bridge the gap between online therapy and real-world outcomes (eg, tips on how to use personal strengths to cope with stress, enhance well-being, or improve social connectedness). Horyzons also includes *peer-to-peer web-based social networking* that includes a web feed (or news feed) where youth with FEP and moderators can post comments and information, upload pictures and videos, and *like* different types of content, and includes *moderation* that is conducted by clinicians and peer support workers.

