### Research and Development of Horyzons and Canadian Adaptations

A detailed description of the intervention, its development, and its subsequent adaptation for the Canadian context can be found in our previous published work [30-32]. The first version of Horyzons was developed iteratively over a 30-month period following participatory design principles involving patients, clinical psychologists, computer programmers, health informatics experts, web and graphic designers, and professional writers. It was then pilot-tested on a sample of 20 young adults for its feasibility, acceptability, utility, and safety considerations over 1 month [27]. Results showed that there were no dropouts and incidents (ie, adverse events or inappropriate use) during the pilot, and system use was high, with a total of 275 log-ins. Specifically, 70% of participants used the system for at least 3 weeks, 95% used the social networking features, and 60% completed at least 3 therapy modules. Moreover, all participants found the system easy-to-use, 70% considered it to be a useful long-term treatment option beyond discharge from early interventions services, 100% considered it to be safe, 85% would recommend it to others, and 100% reported moderation to be helpful. With respect to potential clinical improvements, 70% considered the therapy modules to be helpful, and 60% reported that Horyzons significantly increased their social connectedness. Paired samples *t* tests also revealed a significant reduction in depressive symptoms at follow-up (d=0.60; *P*=.02) [27]. The safety strategy pertaining to the intervention study addressed both static (eg, personality trait variables) and dynamic factors (mental health status), and results indicated no clinical or security problems related to the use of Horyzons during the pilot study [27,33]. Additionally, a second version of Horyzons was evaluated in Australia within the context of a 5-year follow-up randomized controlled trial [29], with results recently published. Horyzons has also been piloted in the United States, and preliminary analyses of within-group effect sizes demonstrated the greatest improvements in psychotic symptoms (d=0.65-0.81), followed by depressive symptoms (d=0.14-0.30) and social functioning (d=0.18) [34]. Horyzons has also been adapted for young people at ultra-high risk for psychosis, and preliminary research suggests that it is effective in improving social functioning in this population [35].

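### The d≥0.5 expectation for social functioning has no stated basis and exceeds the article's own 0.18; at n=20, judging efficacy by whether the point estimate passes 0.5 says little

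*Protocol article*

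**What the plan says.** The third objective in the protocol article (Objectives and Hypotheses) is potential efficacy. Its hypothesis is "Participants will show moderate to large improvements (Cohen *d*≥0.5) on measures of social functioning", naming SOFAS and PSP. The Clinical Global Impression Scale joins them in the same sentence, with no deterioration accepted as success on that scale. The hypothesis is labelled secondary for the study, but these measures are assessed "from baseline to 8 weeks follow-up, as our primary foci for assessing potential efficacy". The same section says the pre-post effect sizes will feed the power calculation of a future trial.

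The section Research and Development of Horyzons and Canadian Adaptations gives the earlier effects:

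- US pilot: "preliminary analyses of within-group effect sizes demonstrated the greatest improvements in psychotic symptoms (d=0.65-0.81"), "followed by depressive symptoms (d=0.14-0.30) and social functioning (d=0.18").
- Original pilot: a larger value, but for a different outcome, namely "a significant reduction in depressive symptoms at follow-up (d=0.60; *P*=.02) [27"].
- Version for ultra-high-risk youth: "preliminary research suggests that it is effective in improving social functioning in this population [35"], with no figure.

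The Analysis Plan section specifies paired t tests, a Bonferroni correction over an unstated number of comparisons, and a minimal clinically important difference still to be determined. It says Cohen d will be reported for the changes that are statistically significant.

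**The concern.** The acceptability percentages in the same section are tied explicitly to the original pilot. The 0.5 for social functioning is tied to nothing, and it is 0.5/0.18 = 2.8 times the one figure the article quotes for that domain. The article does not comment on the gap.

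Two things are at stake. First, if SOFAS and PSP are read by whether the observed d reaches 0.5, a sample of 20 gives an unreliable answer whichever effect is true. Second, the rule of reporting d for significant changes would remove the small and uncertain estimates that the next trial's sample-size calculation needs, and would keep only large ones.

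**Working it through.** The article gives no power or precision calculation for this hypothesis, so there is no figure of its own to reproduce.

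**Inputs**

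- Threshold: d=0.5 (Objectives and Hypotheses).
- Earlier effect: within-group d=0.18 (Research and Development of Horyzons and Canadian Adaptations).
- n=20 analysed, none lost at 8 weeks (Results). The target was 20 to 25.
- Assumptions, because the article does not state them: d is mean change divided by the SD of change; alpha is 0.05 two-sided.

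**Chance that the observed d reaches 0.5**

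The observed d equals t/√n, so d≥0.5 means t ≥ 0.5×√20 = 2.236, where t is noncentral with 19 df and noncentrality (true d)×√20.

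| True d | Noncentrality, n=20 | P(observed d≥0.5), n=20 | n=25 |
|---|---|---|---|
| 0.18 | 0.805 | 9.3% | 6.9% |
| 0.30 | 1.342 | 20.8% | 18.0% |
| 0.50 | 2.236 | 51.1% | 51.0% |

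A miss occurs 1 − 0.093 = 91% of the time if the true d is 0.18, and still 1 − 0.511 = 49% of the time if the hypothesis is exactly right. A miss therefore hardly separates the two. A pass separates them better (51.1/9.3 = 5.5), but the interval around a pass remains wide, as shown next.

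**Precision at n=20** (95% CI by inverting the noncentral t)

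- Observed d=0.18: -0.26 to 0.62, which includes both 0 and 0.5.
- Observed d=0.50: 0.03 to 0.96, which includes 0.18.

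**Sensitivity to the definition of d**

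If d is standardised by a common pre/post SD, the value on the SD-of-change scale is d/√(2(1−r)), where r is the pre-post correlation (assumed 0.3 to 0.9). With a true d of 0.18 and n=20, the chance of observing at least 0.5 runs from about 13% (r=0.3) to 0.7% (r=0.9). With a true d of 0.5 it stays at 51% to 52%.

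**Effect of the reporting rule**

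The smallest significant |d| is t_crit/√n. At n=20 this is 2.093/4.472 = 0.468 unadjusted. With Bonferroni it is 0.544 for 2 tests and 0.710 for 10 tests (numbers of tests assumed). Hence:

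- an observed 0.18 would not be significant and its d would not be reported;
- any d that is reported would be at least 0.468/0.18 = 2.6 times the earlier figure;
- with two corrected tests, an observed d between 0.50 and 0.54 would meet the hypothesis and still go unreported.

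**Why this matters for planning**

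As an illustration, a paired t test with 80% power needs n=34 at d=0.5 and n=245 at d=0.18.

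**The case against.** The strongest reply is that an ambitious, falsifiable prediction is not an error. If the true effect is 0.18, not confirming a moderate-to-large improvement is the correct result. This stands. A reader might infer that the threshold gives the wrong answer, or that the platform would be judged unpromising for performing as it did before. The article does not support that: acceptability has an explicit decision rule and efficacy has none. The sample-size section says efficacy testing is not the main objective, and Strengths and Limitations concedes that 20 participants without a control group may not show effects.

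The 0.18 is also thin evidence. It comes from analyses called preliminary, and the article gives no scale, sample size, duration or definition of d for it. The ultra-high-risk statement points the other way, though without a figure and in another population. So 0.18 cannot be declared the expected effect.

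A further tempting reading is that stable functioning is the platform's aim and would count as failure. The article describes the platform as "designed to sustain the treatment benefits of early intervention for psychosis and to promote long-term social functioning", which is both maintenance and promotion. The entry criterion concerns symptomatic stability, not functioning, so room for functional gain remains. Nor does the article show that this outcome or time frame is the least able to change: the depression range in the US pilot starts lower, at 0.14.

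Finally, a condensed article may leave the rationale for 0.5 to the full protocol, so the missing source alone carries little weight. What these replies leave untouched is the weakness of a point-estimate cut-off at n=20 and the conflict between reporting d for significant changes and needing the effect sizes for planning.

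**Conclusion.** The concern holds in a limited form. The expectation of d≥0.5 is unexplained beside the article's only figure for the domain, 0.18. At n=20, whether the observed d passes 0.5 is a poor summary: about 9% of samples pass if the true d is 0.18, and about 51% if it is 0.5. Read literally, the reporting rule would also withhold d for either scale whenever |d| is below 0.47, or below a higher bound after Bonferroni. These figures assume d standardised by the SD of change and a two-sided 0.05 level; the range under another standardisation is given above. The finding concerns how the estimates are reported and read. It does not show that 0.5 is wrong, that 0.18 is the true effect, or that any decision would be misdirected.

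**What to change.** Keep d≥0.5 only as a stated expectation, and add a sentence acknowledging that it exceeds the cited 0.18, with the reason if there is one. For SOFAS and PSP, report mean change and d with 95% confidence intervals whatever the significance, and say how d is standardised. Interpret both scales against the minimal clinically important difference already planned in the Analysis Plan and against the earlier 0.18, not by whether the point estimate passes 0.5.

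No new data are needed. The cost is a less clear-cut statement on efficacy. Because data collection ended on April 29, 2019, the change must be labelled as made after data collection. For the same reason the 0.5 should stay visible: removing it now could look like a post hoc relaxation.

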### Conclusions

Considering daily use of ICTs among young people and an increasing need for new models of mental health service delivery in the context of the COVID-19 pandemic, research on digital health innovations such as online psychosocial interventions are needed to prevent relapses and support long-term recovery in young people experiencing FEP. However, limited attention has been given to how digital health innovations can be implemented and evaluated in Canada in the context of early interventions for psychosis. In this study, we have reported on the protocol for pilot-testing HoryzonsCa as a follow-up to our phase 1 adaptation study [30,31]. Specifically, this pilot study will provide preliminary evidence on the acceptability (including actual use), safety, and potential efficacy of HoryzonsCa for Canadian young adults with FEP, and an in-depth understanding of user experience and perspectives of HoryzonsCa (eg, perceived barriers and facilitators to using the platform). Our pilot study will inform the development of a research protocol (eg, including pre-post effect sizes on a number of variables conceptually targeted by the intervention, statistical power calculation, or sample size) for a larger implementation study of HoryzonsCa and that also considers sociotechnical factors pertaining to implementation as well as the experiences and perspectives of clinicians and peer support workers on moderating the intervention.

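### Within-group pre-post effect sizes, reported only when significant, are earmarked for powering a future randomized trial, although they are not between-arm effects and are likely to make that trial too small

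*Protocol article*

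**What the plan says.** Objective 3 (Objectives and Hypotheses) concerns potential efficacy. It hypothesises that "Participants will show moderate to large improvements (Cohen *d*≥0.5) on measures of social functioning", and adds that "The analysis will help determine pre-post effect sizes on a number of variables conceptually targeted by the platform". The next sentence fixes what they are for: "These effect sizes will be used in a future clinical trial (eg, randomized controlled trial) for the purpose of statistical power calculation". The Conclusions at the end of the Discussion repeat the intention for a larger implementation study, listing what the pilot will feed into its protocol: "including pre-post effect sizes on a number of variables conceptually targeted by the intervention, statistical power calculation, or sample size".

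The Analysis Plan specifies paired t tests with Bonferroni correction and says that within-group d "will be reported for statistically significant changes between baseline and the 8 weeks follow-up". It also plans a minimal clinically important difference, but for judging change over time, not as the target of a later trial.

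Study Design and Setting and Strengths and Limitations describe a single group with no control. The recruitment and orientation section states that the platform was added to the services participants already received.

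**The concern.** A parallel-group trial is powered on the difference between arms. A single-group change is a different quantity. Here it combines any platform effect with ongoing specialized care, the natural course of illness and repeat assessment. Patients in a control arm on the same services would show much of that change too, so it does not count towards the between-arm difference.

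A second problem comes from the reporting rule. If d is given only where the paired test is significant, small estimates drop out and the surviving values overstate even the within-group change. This happens whatever a control arm would do.

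The stake is the next trial. A target difference taken from these values would probably be too large and the trial too small to detect a realistic effect.

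**Working it through.** **Starting point.** There is no power-based figure to reproduce. The target of 20 to 25 rests on recruitment feasibility, moderator budget and enough active users, and no size is stated for the future trial.

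**Inputs from the article.** Analysed sample n = 20 (Results). Hypothesised d = 0.5 (objective 3). Paired t tests, Bonferroni, d reported only for significant changes (Analysis Plan). Potential Efficacy names 11 instruments.

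**Inputs assumed.** Two-sided 5% level; 1 to 11 tests, since the number is not stated; for the future trial 80% power and 1:1 allocation; d computed as mean change divided by the SD of change. The earlier Horyzons pilot fits that last convention: d = 0.60 with n = 20 gives t = 0.60 × √20 = 2.68 and P = 0.015, in line with the printed .02.

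**1. Precision.** For an observed paired d of 0.50 with n = 20, t = 0.50 × √20 = 2.24 on 19 df. The noncentral t distribution gives a 95% CI for d of 0.03 to 0.96.

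**2. Reporting only significant changes.** The smallest reportable d is t(crit, 19 df)/√20. The mean reported d is from simulation (n = 20, 200,000 replicates).

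| Tests | t(crit) | Smallest reportable d | Mean reported d if true d = 0.3 | Mean reported d if true d = 0.5 |
|---|---|---|---|---|
| 1 | 2.093 | 0.47 | 0.63 | 0.69 |
| 3 | 2.625 | 0.59 | 0.73 | 0.78 |
| 11 | 3.216 | 0.72 | 0.85 | 0.89 |

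With 3 or 11 tests, an observed d of exactly 0.50 would meet the study's own hypothesis and still not be reported.

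To show what this does to a sample size, use the normal approximation n per arm = 2(1.96 + 0.84)²/d² ≈ 15.7/d². A d of 0.63 gives 15.7/0.397 ≈ 40 per arm; a d of 0.3 gives 15.7/0.09 ≈ 174. That gap comes from selection alone, before any change in a control arm is considered.

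**3. Change in the control arm.** Take d = 0.50 as the between-arm effect: 64 per arm (two-sample t). Let controls change by c in the same SD units (c assumed), so the between-arm effect is 0.50 − c.

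| Control change c | Between-arm d | Power at 64 per arm | n per arm needed |
|---|---|---|---|
| worsens by 0.2 | 0.70 | 98% | 34 |
| worsens by 0.1 | 0.60 | 92% | 45 |
| 0 | 0.50 | 80% | 64 |
| improves by 0.1 | 0.40 | 61% | 100 |
| improves by 0.2 | 0.30 | 39% | 176 |
| improves by 0.3 | 0.20 | 20% | 394 |

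**4. Scale of d.** With pre-post correlation r (not given), a paired d of 0.50 equals 0.50 × √(2(1 − r)) in units of the between-person SD. At r = 0.8 this is 0.32 (0.316 unrounded). An unadjusted comparison of follow-up scores would then need 158 per arm. A change-score analysis keeps d = 0.50 and 64 per arm. ANCOVA, with residual SD multiplied by √(1 − r²), needs 42 to 61 per arm for r = 0.3 to 0.9. The scale therefore causes undersizing only under one analysis and only when r exceeds 0.5.

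**The case against.** The best defence is that the sentence concerns a study not yet designed, with a randomized trial given only as an example. It changes no analysis or conclusion of this pilot. The article says efficacy testing is not the main objective and names the small sample and missing control group as limitations. It also collects recruitment and feasibility data for the next study. This is a good reason to lower the severity, but it does not remove the point. The limitations text warns only that effects may be missed. It does not address shared change being credited to the platform, or the estimate being carried into a power calculation.

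The direction of error can also be disputed. Participants had to be symptomatically stable at entry, the Background describes relapse and difficulty in sustaining gains, and the platform aims to sustain treatment benefits. Controls might therefore stay level or worsen. That stands: in those cases 64 per arm is enough or more than enough.

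A reader might infer several stronger points that the documents do not support:

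- **A large undersizing from the SD of change alone (64 against 158 per arm).** This needs r = 0.8 and a later analysis that ignores baseline. The article fixes neither, nor the denominator of d, and the effect disappears with ANCOVA or change scores.
- **Unblinded-rater effects as something a control arm would share.** Raters who know the allocation can favour the active arm, so these effects need not cancel.
- **The Australian trial as a ready target difference.** The article says that "a second version of Horyzons was evaluated in Australia within the context of a 5-year follow-up randomized controlled trial" but gives no result from it, so its suitability for an 8-week outcome cannot be judged here.
- **A fault in the transformation clause.** Transformation is conditional, and choosing it over a bootstrap or rank test is a matter of preference.

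**Conclusion.** The point holds in limited form. The article commits within-group effect sizes from an uncontrolled pilot to a power calculation that needs a between-arm effect, and its reporting rule selects those values upward. Both follow from the text. The selection figures assume a two-sided 5% level, d on the SD of change and 1 to 11 tests.

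Undersizing is the likely result, because controls would probably receive the same active services and because of the selection. It is not certain: control-arm change, pre-post correlation, the formula for d and the later analysis are all unstated. Even without selection, the interval of 0.03 to 0.96 around an observed d of 0.50 is too wide to serve as a design input.

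Severity is moderate. The primary acceptability objective and the safety assessment do not depend on this use of the effect sizes.

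**What to change.** Change the wording in three places.

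- **Objectives and Hypotheses, objective 3, and the closing Conclusions:** state that the pilot will supply the SD, pre-post correlation, recruitment, retention and platform use for the future trial. State that the trial's target will be a minimally important between-arm difference, and that the within-group d will not serve as that target.
- **Analysis Plan:** report every pre-post effect size, significant or not, with its denominator and 95% confidence interval.

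No new data are needed, and the article describes analysis and reporting as still in process. The cost is that the future trial's stated size may be larger, and the results report will show more wide intervals.
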